## Abstract

**Background:**

Studies have consistently indicated that the majority of individuals meeting the US Prevention Services Task Force guidelines for genetic testing have not had genetic counseling or testing. Despite increased availability and lower costs of multiplex cancer gene panels, there remains a gap in genetics services that has not been addressed by the current care delivery models. Lower cost of DNA sequencing with online patient-initiated ordering could increase test availability, but the ideal quantity and delivery method of patient education is not known. We hypothesized that online genetic education and testing with access to board certified genetic counselors could improve access to genetic testing while maintaining test quality and clinical utility. The MAGENTA (MAking GENetic Testing Accessible) trial is a nationwide randomized study designed to compare the effectiveness of online genetic education with pre- and post-test telephone genetic counseling to three potentially more accessible alternative approaches: online genetic education with optional telephone counseling, online genetic education with required pre-test telephone genetic counseling, and online genetic education with required post-test telephone genetic counseling.

**Methods:**

3000 women nationwide will undergo genetic testing for 19 hereditary cancer genes. This is a randomized four-arm non-inferiority study with equal randomization. The four study arms were selected to independently assess the delivery of genetic information both before and after genetic testing (pre-test and post-test) by either requiring telephone genetic counseling or providing only online education with optional telephone counseling. Patients have post-test telephone counseling when testing positive for a pathogenic inherited mutation in all four arms. Surveys measuring psychological, behavioral and cognitive state are completed online at baseline, 3 months, 12 months and 24 months post-results disclosure. The primary study outcome is cancer-risk distress at 3 months post-result disclosure.

**Discussion:**

This trial will assess the use of a genetic service model using online access and electronic education, while evaluating the need for personal pre- and post-test genetic counseling. Data from this study may lead to increased options for delivery of genetic testing and possibly increase access to genetic testing. Identifying more individuals with inherited cancer susceptibility will allow targeted cancer prevention.

**Trial registration:**

Clinicaltrials.gov: NCT02993068 (registered December 14, 2016).

## Background

Rapid developments in cancer genetics over the past decade have changed the landscape of genetic testing for hereditary cancer. The availability of next generation sequencing, coupled with the Supreme Court decision invalidating patents on human genes, has led to substantially decreased cost of germline testing and has created a shift from single syndrome or gene by gene testing to multiplex gene panel testing. Identification of individuals who carry a mutation in cancer predisposition genes such as *BRCA1* and *BRCA2* allows for prevention and early detection.

However, studies have consistently indicated that the majority of individuals meeting the United States Prevention Services Task Force (USPSTF) guidelines for genetic testing have not had genetic counseling or testing [1]. Childers and colleagues estimate that over 1.2 million women with a history of breast and/or ovarian cancer have not undergone genetic testing despite meeting evidence-based guidelines for testing [2]. Cascade testing is the process of testing biological relatives of individuals who have been identified to have a genetic mutation. Cascade testing for inherited cancer risk has been identified as a public health priority by the Centers for Disease Control and Prevention (CDC), but uptake of cascade testing is low, with only 30% of eligible first-degree relatives receiving testing [3]. These findings indicate that despite increased quality and lower costs of multiplex cancer gene panels, there remain important barriers to genetic testing.

Various service delivery models (SDMs) have been explored and adopted to increase access to cancer genetic testing services. The traditional SDM for cancer genetic testing employs in-person pre-test and post-test genetic counseling. Telephone genetic counseling has been shown to be non-inferior to in-person counseling and is now a widely accepted SDM with the potential to provide services to patients who live far from genetics specialists [4, 5]. Online genetic testing services are now commercially available but the amount, type and degree of personalization of paired education and counseling required in order to optimize patient understanding and minimize distress is unknown.

### Proposed alternate remote testing service delivery model

Online access to physician ordered genetic testing for clinically actionable hereditary cancer genes has the potential to increase access to genetic testing while maintaining test quality and clinical utility. Smit and colleagues found that individuals believe online communication is an acceptable mode of receiving medical information, and that it is important to have a health professional available to discuss questions and content as needed [6]. One study has examined the use of online genetic testing for cascade testing of family members and found it to be an effective approach to implementing cascade testing, citing an uptake of cascade testing in 47.5% of first degree relatives [7].

The availability of online genetic education detailing the benefits and limitations of hereditary cancer testing with access to board certified genetic counselors offers a promising alternative that may overcome barriers faced by current SDMs. Such a model could allow both genetics and non-genetics clinicians to order genetic testing while providing patients with detailed online information regarding hereditary cancer testing, overcoming the major barriers of physician coordinated testing, including limitations of physician time and knowledge. Remote access testing may eliminate the major barriers of in-person counseling, including time and money spent on travel, while increasing flexibility and accessibility, which continue to be challenges of both in-person counseling and telephone counseling. Remote access genetic testing via the use of an online genetic services platform allows individuals to access information using the internet with the ability to revisit if they choose, avoiding the need for appointments and allowing for patient-driven and convenient genetic services. Electronic copies of genetic test results may be shared easily with family members and medical providers. For individuals found to have a pathogenic mutation, online platforms facilitate easy information sharing, and the option of online access to testing services may promote the uptake of cascade testing in blood relatives.

One question in this proposed SDM is how much personalized counseling is needed both pre-test and post-test to optimize patient outcomes. Does required personalized counseling reduce patient distress and improve understanding or does it add unnecessary cost and time and reduce likelihood of test completion? Is pre- or post-test counseling more important and if counseling is provided as an option, how many patients will utilize telephone counseling, and can we identify patient subsets who have greater benefit from personalized counseling? To address these considerations, we are conducting a prospective study to evaluate different amount of personalized genetic counseling within an online genetic testing model to determine less counseling is non-inferior to our current accepted SDM at delivering hereditary cancer risk information. The purpose of this paper is to describe the design of the MAGENTA study, a prospective randomized trial of online genetic education vs telephone genetic counseling for hereditary cancer genetic testing.

## Methods/design

### Study aim and hypothesis

The MAGENTA (MAking GENetic Testing Accessible) trial is designed to compare the effectiveness of pre- and post-test telephone counseling to three potentially more accessible alternatives for individuals undergoing analysis of 19 hereditary breast and ovarian cancer (OC) genes. The genes included are: *ATM, BARD1, BRCA1, BRCA2, BRIP1, CDH1, CHEK2, EPCAM, MSH2, MSH6, MLH1, NBN, PALB2, PMS2, PTEN, RAD51C, RAD51D, TP53,* and *STK11*. Our primary hypothesis is that the outcomes for subjects receiving one of the three alternative approaches utilizing genetic education online will not be inferior to those of participants receiving a current acceptable standard of telephone genetic counseling both pre- and post-testing [4, 5].

### Study design

After online eligibility screening and electronic study consent (as approved by the Human Subjects Division of the MD Anderson Institutional Review Board), randomization into one of four study arms is performed automatically using a web-based data management platform [8]. The four study arms were selected to independently assess the delivery of genetic information both before and after genetic testing (pre-test and post-test) by either telephone genetic counseling or online education alone. The control arm requires mandatory pre and post-test telephone counseling while the other three arms provide various combinations (Table 1). Participants are mailed a saliva collection kit after all pre-test online education and/or genetic counseling is completed, based on study arm. Analysis of 19 OC genes is completed once the participant returns the saliva sample. As an additional safety measure, any participant found to carry a pathogenic or likely pathogenic mutation has required post-test telephone counseling and any participant desiring genetic counseling is provided with telephone genetic counseling regardless of study arm. A study schema can be found in Fig. 1. Participants were stratified into one of two risk groups: individuals with a personal and/or family history of cancer, and those with a known familial mutation (cascade group).

**Table 1 Tab1:** Study Arms

	Pre- Genetic Testing	Post- Genetic Testing
Arm A	Online educational video	Online Test Results Report
Arm B	Online educational video	Online Test Results Report + Telephone Genetic Counseling
Arm C (Control)	Online educational video + Telephone Genetic Counseling	Online Test Results Report + Telephone Genetic Counseling
Arm D	Online educational video + Telephone Genetic Counseling	Online Test Results Report

Note: optional telephone genetic counseling is allowed at any point in all arms at patient request and is mandated post-test for all patients with pathogenic mutation regardless of study arm

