### Statistical considerations

We employ a non-inferiority design with a non-inferiority margin of 4 points, as suggested by Schwarz et al. (2014), for the difference in IES score between the control arm and each of the other three study arms at 3 months post-result disclosure.

We are enrolling 5200 eligible women with a goal of 3000 completing genetic testing. We expect that around 85% (*n* = 4400) of those who consent to participate will complete the baseline questionnaire and then be randomized. Of these, we will enroll around 750 subjects with a known familial mutation into the cascade group, with the remaining 3650 subjects, who have an increased likelihood of carrying a deleterious mutation in an ovarian cancer predisposition gene based on personal and family history of disease, as the group of interest for our primary analysis. We expect that 65% (*n* = 2375) of the 3650 participants with personal and/or family history of disease will follow through with providing a saliva sample for analysis, with 75% of those subjects completing the study through the 3 month assessment (*n* = 1780), which equates to about 450 participants on each of the four study arms.

Each of the three experimental study arms will be compared to the control study arm using a one-sided t-test, with the null hypothesis for each of the three tests that the mean stress score in the experimental arm is more than 4 points above the mean stress score in the control arm. A one-sided significance level of 0.025 is targeted across all three tests, resulting in a Bonferroni-corrected significance level of 0.0083 for each test. The sample size was chosen to achieve 93% power for each test, assuming a standard deviation in the scores of 15.3 based on Schwartz et al., yielding an overall power of 80%.

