Our secondary outcome is the “completion rate”, defined as a participant progressing through the entire process from pre-test genetic education/counseling to receiving their test results and post-test genetic education/counseling. We will test two null hypotheses regarding the completion rate: that the completion rate for the participants receiving only online genetic education before testing (Arms A and B) is more than 6% less than it is for participants who were randomized to receive telephone genetic counseling before testing (Arms C and D), and that the completion rate for the participants receiving only online genetic education after testing (Arms A and D) is more than 6% less than it is for participants who were randomized to receive telephone genetic counseling after testing (Arms B and D). This 6% non-inferiority margin is more conservative than the 7.5% margin used by Schwartz et al. [5].

In addition to testing our primary and secondary hypotheses, we will summarize for each study arm the key outcomes related to cognition, affect and behavior, and the changes in scores from baseline. We will also use regression models to model the scores (and changes in the scores from baseline) as a function of study arm, risk group, and other covariates.

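### For 3-month distress, the 2x2 layout of the arms is analysed only arm by arm against control; averaged pre-test and post-test effects, their interaction and the B-D comparison are not specified

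*Protocol article*

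**What the plan says.** - **Purpose of the arms.** Protocol article, Study design: "The four study arms were selected to independently assess the delivery of genetic information both before and after genetic testing (pre-test and post-test"). Table 1 crosses pre-test telephone counseling (required or not) with post-test telephone counseling (required or not): A neither, B post-test only, C both (control), D pre-test only.
- **Motivating question.** The section on the proposed alternate remote testing model asks: "Is pre- or post-test counseling more important".
- **Primary hypothesis.** Study aim and hypothesis: "Our primary hypothesis is that the outcomes for subjects receiving one of the three alternative approaches utilizing genetic education online will not be inferior". The comparator is telephone counseling at both stages.
- **Primary analysis.** Statistical considerations: "We employ a non-inferiority design with a non-inferiority margin of 4 points" and "Each of the three experimental study arms will be compared to the control study arm using a one-sided t-test". On multiplicity, the overall one-sided level of 0.025 is divided among the comparisons, "resulting in a Bonferroni-corrected significance level of 0.0083 for each test".
- **Other analyses.** The same section compares completion on pooled arms, one contrast per stage. For the scores it adds regression models "as a function of study arm, risk group, and other covariates". It names no factor contrast, interaction or B-D comparison for IES.

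**The concern.** The stated reason for choosing these four arms is a two-factor question: what does telephone counseling contribute before testing, and what does it contribute after? The secondary outcome is analysed that way and the primary outcome is not. For distress, the plan specifies the effect of dropping pre-test counseling only where post-test counseling is kept (B-C), and the effect of dropping post-test counseling only where pre-test counseling is kept (D-C). The matching contrasts at the other level, A-D and A-B, have no named role.

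Three things are at stake: the precision of the stage effects, whether the effect of one stage depends on the other, and a prespecified answer to which stage matters more. If the contrasts are not named in advance and appear in the report, they will look chosen after the fact.

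**Working it through.** **Inputs.** From Statistical considerations: SD 15.3, margin 4 points, one-sided level 0.025/3 = 0.0083 per test, and 1780 women assessed at 3 months, so 1780/4 = 445 per arm (the article rounds to about 450). Allocation is equal (Abstract, Methods). The true difference behind the power figure is not stated; I assume 0.

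**The plan's own figure.** Pairwise SE = 15.3 × √(2/445) = 1.026. Power = Φ(4/1.026 − 2.394) = 0.934 at 445 per arm, and 0.937 at 450. The stated 93% is reproduced.

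**Contrasts available from the 2x2.** Let A, B, C, D be the arm means of IES, where a positive contrast means more distress with less counseling.

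| Quantity | Contrast | SE at 445 per arm | 95% half-width |
|---|---|---|---|
| Pre-test effect, post-test kept | B − C | 15.3 × √(2/445) = 1.03 | 2.01 |
| Post-test effect, pre-test kept | D − C | 1.03 | 2.01 |
| Averaged pre-test effect | (A+B)/2 − (C+D)/2 | 15.3 × √(2/890) = 0.73 | 1.42 |
| Averaged post-test effect | (A+D)/2 − (B+C)/2 | 0.73 | 1.42 |
| Interaction | (A−D) − (B−C) | 15.3 × √(4/445) = 1.45 | 2.84 |
| Pre-test minus post-test effect | B − D | 1.03 | 2.01 |

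These are unadjusted standard errors. At 450 per arm they are 1.02, 0.72 and 1.44.

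**What averaging gains.** The averaged pre-test effect is the mean of B−C and A−D. The averaged post-test effect is the mean of D−C and A−B. Each uses about 1780 women instead of 890, which halves the variance.

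**What averaging does not gain.** For which stage matters more, subtract one averaged effect from the other:

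[(A+B) − (C+D)]/2 − [(A+D) − (B+C)]/2 = B − D.

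This also equals (B−C) − (D−C). Its SE is the pairwise 1.03 either way.

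**Why the 4-point margin does not carry over.** Adding the two averaged effects gives

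[(A+B) − (C+D)]/2 + [(A+D) − (B+C)]/2 = A − C.

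Two averaged effects each just under 4 points are thus compatible with arm A being nearly 8 points worse than control. The margin is stated for an arm against control, and passing it on both factors would not show that A passes it.

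**The case against.** The case for leaving the plan as it stands is substantial.

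- **The primary tests match the primary hypothesis.** Each alternative is compared with control, as the hypothesis says. No assumption about interaction is needed, and the stated power reproduces. This stands, and it is why those tests should remain primary.
- **Both stages are already estimated.** A reader might infer that neither the pre-test nor the post-test question is estimated for distress. The documents do not support that: B-C and D-C are randomized estimates of dropping each stage.
- **All arms are used.** A reader might also infer that half the data go unused. They do not, because A is tested against C. The factor of two applies only to the variance of a stage effect.
- **The regression can already deliver the contrasts.** A model with pre-test mode, post-test mode and their interaction has the same fit as one with a four-level arm term. This is correct, so the fix requires naming contrasts and not fitting a new model. The full protocol or analysis plan may name them. Still, the article sets out the IES analysis in some detail and gives factor margins for completion only, so the mismatch with its stated purpose is visible in the text.
- **Pooling does not sharpen which stage matters more.** This is also correct, as the algebra shows. What is missing there is a named B-D estimate.

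**Conclusion.** The point holds as a gap between the stated purpose of the arms and the analysis named for the primary outcome. The cost is precision and completeness; no error rate is affected and no stated figure is wrong. For 3-month IES, each stage effect is specified only with the other stage's counseling kept, at an SE of about 1.03. An averaged effect would have an SE of about 0.73, making its interval about 29% narrower (1 − 1/√2). The interaction and B-D are not specified.

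The figures assume 445 women per arm at 3 months and a common SD of 15.3. An averaged effect reads cleanly only if the interaction is small, and with an SE of about 1.45 the trial can judge that only roughly. It would be tempting to go further and present the averaged effects as better-powered non-inferiority tests. The documents do not support that, because the 4-point margin is set for an arm against control.

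**What to change.** Keep the three arm-versus-control tests as primary, with the margin, significance level and sample size unchanged. In the regression already planned for the scores, prespecify for 3-month IES, as supportive estimates with confidence intervals:

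1. the pre-test contrast, A+B versus C+D;
2. the post-test contrast, A+D versus B+C;
3. the interaction, (A−D) − (B−C);
4. B − D, as the comparison of the two stages.

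State that these are not tested against the 4-point margin, that the averages are to be read alongside the interaction, and that they do not establish non-inferiority of A to C. Take the post-test grouping from Table 1 (B and C receive required post-test counseling); the completion paragraph prints B and D for that group, which conflicts with the table.

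The cost is wording only: no new data, no extra participants and no change to the primary error rate. The article describes the trial as ongoing, so the contrasts should be fixed before the 3-month IES data are compared by arm.

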**Fig. 1 Fig1:**
[figure not shown]
MAGENTA study schema

### Study population

The MAGENTA study’s target population is women that may be at increased risk to develop ovarian cancer based on their personal or family history of cancer or due to a known cancer susceptibility gene mutation in the family. Women must be 30 years of age or older and must have at least one ovary, as we hope to identify women who will be able to take actionable measures to reduce ovarian cancer risk. As a safety precaution, all participants are required to identify a local healthcare provider with whom their genetic test results will be shared. Complete eligibility criteria are outlined in Table 2. Approximately 5200 women will be enrolled with a goal of 3000 completing genetic testing. We estimate that we will need to screen between 7000 and 10,000 women using an online eligibility questionnaire.

**Table 2 Tab2:** Eligibility Criteria

*Inclusion Criteria*	
*Participants must meet each of the following four criteria*	
1) Women ages 30 or older	
2) Have access to a healthcare provider and be willing to share genetic results with that provider	
3) Have at least one ovary	
4) Have a valid United States mailing address for receipt of saliva kit	
*Additionally, participants must also meet any one of the following six criteria:*	
5) Diagnosed with breast cancer at age 45 or younger	
6) Diagnosed with triple negative breast cancer at age 60 or younger	
7) Have one biological relative with a mutation in BRCA1, BRCA2, BRIP1, PALB2, RAD51C, RAD51D,	
BARD1, MSH2, MSH6, MLH1, or PMS2	
6) Have a biological relative with ovarian cancer	
7) Have at least 2 biological relatives with breast cancer on the same side of the family, one of which is < age 50	
8) Have one biological male relative with breast cancer	
*Exclusion Criteria*	
1) Personal history of ovarian cancer	
2) Unable to speak English	
3) Unable to provide informed consent	
4) Unwilling to complete baseline and follow-up questionnaires	
5) Unable to access the internet	
6) Previous genetic testing or counseling regarding cancer risk	
7) Previous bone marrow transplant	
8) Previous blood transfusion (7 days prior to genetic testing)	
9) Active hematologic malignancy	
10) Residents of the state of New York	

Recruiting efforts are being carried out through clinical settings, advocacy groups, and various social media platforms. The different recruitment strategies were designed to capture a heterogeneous group of women, which will allow us to assess whether we improve access to genetic testing in diverse patient populations stratified for race and ethnicity, as well as, socioeconomic, educational and geographical backgrounds.

